#### Data collection and follow-up

Baseline characteristics will be recorded immediately after inclusion, including age, gender, primary diagnosis, PaO_2_/FiO_2_, causes of ARF and immunocompromised status, preexisting comorbidities, SAPS II, oxygen therapy and other treatment used before the inclusion. The information required for evaluation during study participation will be recorded daily until primary endpoint occurs or until day 30 after inclusion, whichever occurs first. Evaluations include settings of intervention, other treatment, laboratory data, evaluation of ARF, adverse events of intervention and complications developed during hospital stay. Each patient is followed until day 60 or until other endpoints occur, whichever occurs first. The following data are recorded: 30-day survival, length of hospital stay, hospital survival and adverse events of intervention.

#### Coordination and conduct of the trial

Ahead of patient recruitment, all physicians and other health-care workers in the seventeen participating hospitals will attend formal training courses on the study protocol and data collection. Data will be recorded in electronic case report form (eCRF), which is a web response system available at each study center. eCRF system is provided and managed by the Emergency Department of Peking Union Medical College Hospital. All documents required for the study are available in each center. In each participating hospital, a medical team leading by at least one senior physician will be in charge of daily patient screening and inclusion, making sure compliance with the study protocol. The principal investigators will meet with the medical teams to evaluate study progress and to discuss any problems with protocol compliance and data collection.

#### Interim analysis

Considering a large estimated sample size, two interim analyses are scheduled. Sample sizes of 176 achieve 90% power to detect a difference of 0.25 between the group proportions of 0.50 and 0.75 at a significance level (alpha) of 0.05 using a two-sided z-test with continuity correction. Assuming a dropout rate of 25%, the subjects were required to be 236. The O’Brien-Fleming spending function will be used to determine the test boundaries for 3 sequential tests (Nominal Alpha = 0.000207, 0.012025, 0.046259) [36]. One interim analysis is scheduled after enrollment of 39 patients in both group, and the second analysis after another enrollment of 39 patients in both groups. The independent data and safety monitoring committee (DSMC) consists of one biostatistician and two physicians independent of the present trial. For both interim analyses, the DSMC will monitor and assess results on day 30 mortality, failure of NIV, severe complications and seven-day organ failure as indicated by the SOFA scores. The results of the interim analyses will be kept closed unless DSMC requests premature trial termination based on these results. If the difference of the main outcome, mortality was found statistical difference between groups, then discontinuation ahead will be applied.

### Statistical analysis

All data will be analyzed based on the intention-to-treat (ITT) principle. All analysis results and findings will be reported according to CONSORT statement recommendations [37]. Descriptive statistics will be used to comparing the baseline features of the groups established by randomization. All tests will use a significance level of 0.05 and be performed using SAS 9.4 (TS level 1 M2; Cary, NC, USA).

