### Sample size

The hypothesis of the present trial is that 30-day all-cause mortality in patients treated with NIV will be lower than those treated with IMV. According to previous studies, the mortality rate of ARF immunocompromised patients is from 30% to 90% [1–4]. We used the data from the Fig. 4 of our previous meta-analysis to calculate the sample size, i.e. 30-day mortality in IMV-treated patients of 125/168 (75%) [21], and 85/168 (50%) [21] in NIV-treated patients, 88 patients are needed in each group to establish non-inferiority with 90% power and a 1-sided 5% type I error rate. Assuming that 25% of patients would be lost after the enrollment, thus at least of 236 patients are required.

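### The protocol gives two different significance levels for the final test of 30-day mortality: 0.046259 under Interim analysis and 0.05 under Statistical analysis

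*Protocol article*

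**What the plan says.** **Interim analysis.** The section states that "two interim analyses are scheduled", so with the final analysis there are three tests of mortality. The overall level is two-sided: "at a significance level (alpha) of 0.05 using a two-sided z-test with continuity correction". An O'Brien-Fleming spending function sets the boundaries, listed as "Nominal Alpha = 0.000207, 0.012025, 0.046259". The third value belongs to the final test. The section closes with the stopping sentence: "If the difference of the main outcome, mortality was found statistical difference between groups, then discontinuation ahead will be applied". That sentence does not name a boundary.

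**Statistical analysis.** The general paragraph says "All tests will use a significance level of 0.05 and be performed using SAS 9.4" and carves out nothing for the primary endpoint.

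**Statistical analysis, Primary endpoint.** Mortality at 30 days is compared by a chi-square test and reported with 95% confidence intervals. No level is named for this test. The only other level in that paragraph is 0.025, for multiple comparisons.

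**The concern.** A group-sequential plan keeps the overall error at 5% by spending a little at each interim look and making the final test slightly stricter than 0.05. An analyst working from the Interim analysis section would use 0.046259 at the end. One working from the Statistical analysis section would use 0.05. The two disagree whenever the final p-value falls between 0.0463 and 0.05.

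At stake is the primary conclusion of a mortality trial. If the choice between two published thresholds is made after the data are seen, it will look data-driven whichever way it goes. The general sentence also offers a competing threshold for the stopping sentence, which speaks only of a statistical difference.

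**Working it through.** **Inputs.** From Interim analysis: three tests, overall two-sided 0.05, levels 0.000207, 0.012025 and 0.046259, looks after 39 and then a further 39 patients per group, 90% power for 0.50 versus 0.75, 176 patients in all, 236 with 25% dropout. From Statistical analysis: 0.05 for all tests.

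**1. Reproduce the listed levels.** Take the Lan-DeMets O'Brien-Fleming-type function with 0.025 per side at information t = 1/3, 2/3, 1. The cumulative two-sided error spent is 4·[1 − Φ(z(1 − 0.0125)/√t)], which gives 0.000207, 0.01210 and 0.0500. Solving for each boundary by recursive numerical integration gives critical values of about 3.710, 2.511 and 1.993. These correspond to nominal levels 0.000207, 0.01202 and 0.04626, so the plan's levels are reproduced.

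**2. Check that the sample size is consistent with them.** With these boundaries, 90% power needs a drift of 3.2606. Using pooled variance, 2 × 0.625 × 0.375 = 0.46875:

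- n = 0.46875 × 3.2606² / 0.25² = 79.74 per group
- with continuity correction, n/4 × [1 + √(1 + 4/(0.25n))]² = 87.56, rounded up to 88, or 176 in all
- 88/0.75 = 117.3, rounded up to 118 per group, or 236 in all

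The same pooled formula without interim looks uses 1.960 + 1.2816 in place of 3.2606. It gives 78.81, or 86.6 after correction: 87 per group, 174 in all. A fixed design with the variance split between null and alternative gives 85 per group, 170 in all. The stated 176 therefore fits the sequential boundaries, but the margin is only one patient per group on the pooled formula. This is supporting evidence and not proof.

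**3. Overall two-sided type I error.** This is the probability, under no difference, of crossing at any of the three looks:

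| Information at looks 1 and 2 | Final level 0.046259 | Final level 0.05 |
|---|---|---|
| 1/3 and 2/3 | 5.00% | 5.35% |
| 78/236 = 33.1% and 156/236 = 66.1% | 5.01% | 5.36% |
| 78/176 = 44.3% and 156/176 = 88.6% | 4.69% | 5.05% |
| 28.9% and 61.9% | 5.07% | 5.42% |

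The third row applies if all 39 and 78 patients per group contribute but only 176 do at the end. The fourth assumes uniform accrual of 236/24 = 9.8 patients a month and a data cut on the day the enrolment target is met, so that about one month's patients lack day-30 status: (78 − 9.8)/236 and (156 − 9.8)/236.

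**4. Cost in power of the stricter final level.** At 88 per group with continuity correction, the drift is (0.25 − 1/88)/√(0.46875/88) = 3.270. Power is 90.2% with 0.046259 and 90.7% with 0.05.

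**The case against.** The strongest reply is that a specific rule outranks a general one. The Interim analysis section sets the third test explicitly, and the sample size is consistent with it. The all-tests sentence is not literal elsewhere either: 0.025 is used for multiple comparisons and p < 0.03 for the logistic model. On this view the document has a missing cross-reference and no error inflation. Much of that stands: 0.046259 is the better-supported reading. It does not remove the contradiction, because those other departures from 0.05 are stated where they apply, while the primary endpoint paragraph states none.

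Three stronger readings are tempting, and the documents do not support them.

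- *That the trial's type I error exceeds 5%.* This follows only if the general sentence prevails, which the protocol does not say.
- *That all three looks would be at 0.05, for about 10.7% overall.* This reads the stopping sentence against the boundaries listed a few lines earlier in the same section. Its natural meaning is significance by those boundaries.
- *That looks timed by enrolment undermine the plan.* The protocol says "One interim analysis is scheduled after enrollment of 39 patients in both group", but not that data are cut on that day. Even with an immediate cut, the listed levels give about 5.07%, and a spending function allows recomputation.

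It may also be said that the Sample size section uses a different benchmark: "88 patients are needed in each group to establish non-inferiority with 90% power and a 1-sided 5% type I error rate". Against a one-sided 5%, a final two-sided test at 0.05 would spend only about 5.35%/2 = 2.7% in the favourable direction. That is a separate conflict. The listed levels are built on the two-sided 0.05, so that is the benchmark here.

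**Conclusion.** The contradiction is real and lies in the current text: 0.046259 in one section and 0.05 in another for the same test. Its numerical effect is small. If 0.05 is followed, two-sided type I error is about 5.35% at equally spaced looks, and about 5.05% to 5.4% over the look timings examined. These figures assume that the interim looks use the listed 0.000207 and 0.012025, that the normal approximation holds, and that the benchmark is the two-sided 0.05 of the Interim analysis section. Only a final p-value between 0.0463 and 0.05 changes the conclusion. The matter deserves correction because it concerns the primary decision rule and costs almost nothing to settle, not because serious inflation has been shown.

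**What to change.** **Statistical analysis section.** Say that the final test of 30-day mortality uses the O'Brien-Fleming level, which is 0.046259 at equally spaced looks and is recomputed from the spending function at the actual information fractions. Say that 0.05 applies to other tests unless another level is stated, which leaves the 0.025 for multiple comparisons intact.

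**Interim analysis section.** Tie the closing sentence to the boundaries: a statistical difference at an interim look means crossing the O'Brien-Fleming boundary for that look. That boundary is 0.000207 at one third and 0.012025 at two thirds of the information, recomputed from the spending function at the information actually available on day-30 mortality. Recomputation should cover the interim levels as well as the final one. If 39 and 78 patients per group have day-30 status and only 88 do at the end, the fractions are 44% and 89%, and the listed values no longer match the function.

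**Cost.** Wording only. The final threshold becomes slightly stricter than 0.05, with power of about 90.2% instead of 90.7% at 88 per group. The sample size does not change.

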#### Primary endpoint

30-day mortality will be reported as frequency with the 95% confidence intervals and compared between the two groups using the χ^2^ test. We will explore the interaction between treatment effect and baseline disease severity indicated by SAPS II (cut-off value 60) and PaO_2_/FiO_2_ (cut-off value 100). If such an interaction is found, we will further conduct subgroup analysis to explore a treatment effect within each subgroup. Multiple comparisons will be conducted with the Bonferroni test (error of first order 0.025). Similar analysis will be conducted between treatment effect and different causes of immunodeficiency (divided into two subgroups: a. solid tumors or hematologic malignancies, b. immunosuppressive treatment or organ transplant.).

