#### Randomization and blinding

Consecutive eligible patients will be randomly allocated in a 1:1 ratio to one of NIV or IMV. This study will include a total of 236 patients. Center 1 to Center 9 will each include 12 patients and Center 10 to Center 17 will each include 16 patients. Because the greatest common divisor of 12 and 16 is 4, we chose the block size 4. For this study, the statistician will produce computer-generated block randomization lists with SAS 9.4 (TS level 1 M2; Cary, NC, USA) stratified on the center. The randomization in blocks will be performed using opaque envelopes containing the IDs of the treatment group (NIV and IMV group). Then we will seal, shuffle the envelopes and number them in sequential order. For each eligible new patient, an envelope will be opened and then disclose the group allocation for this patient. The randomization day will be recorded as the study day zero (T0). We apply the PROBE Design [35] because ventilation cannot be blinded, and an effective sham measure is not available. Blinding to allocation of groups will be applied to the analysis.

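### The primary mortality test is valid but leaves the centre strata and the recorded baseline severity unused, at a modest cost in power

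*Protocol article*

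**What the plan says.** The Primary endpoint paragraph under Statistical analysis fixes the test: "30-day mortality will be reported as frequency with the 95% confidence intervals and compared between the two groups using the" chi-square test. It mentions no adjustment.

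Under Randomization and blinding, patients are "randomly allocated in a 1:1 ratio to one of NIV or IMV", with lists "stratified on the center" in blocks of 4. The centre sizes are given: "Center 1 to Center 9 will each include 12 patients and Center 10 to Center 17 will each include 16 patients".

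Under Data collection and follow-up, "Baseline characteristics will be recorded immediately after inclusion, including age, gender, primary diagnosis, PaO_2_/FiO_2_, causes of ARF" and, later in the same list, "preexisting comorbidities, SAPS II, oxygen therapy and other treatment used before the inclusion". Both severity measures are therefore collected for every patient.

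For mortality, the plan uses them only in exploratory interactions and subgroups: "We will explore the interaction between treatment effect and baseline disease severity indicated by SAPS II (cut-off value 60"), and the same sentence adds PaO2/FiO2 with a cut-off of 100. The Secondary endpoints paragraph does force disease severity into a logistic model, but that model is for intubation and weaning rates.

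**The concern.** The protocol treats severity as central. The Background says the benefit of NIV depends on it, and the secondary goal is to estimate effects by severity. A baseline variable that predicts death can sharpen the treatment comparison at no cost in patients or visits, and the primary test does not use it. Nor does the test follow the stratification used to randomise.

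What is at stake is power if the true effect is smaller than planned. The 25-point design difference comes from the sponsor's meta-analysis of 13 observational studies, whose evidence the Background grades very low to moderate. A true difference of 15 to 20 points is a reasonable case to plan for, and that is where adjustment pays most.

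**Working it through.** **1. The plan's own sample size.** Inputs (Sample size; Interim analysis): mortality 0.75 v 0.50, 90% power, two-sided test with continuity correction, final-look nominal alpha 0.046259, 25% dropout.

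- Uncorrected: n = [z(1-α/2)·√(2·p̄·(1-p̄)) + z(0.90)·√(p1(1-p1)+p2(1-p2))]² / d², with p̄ = 0.625 and d = 0.25. At α = 0.046259: (1.993 × 0.6847 + 1.2816 × 0.6614)² / 0.0625 = 78.3.
- Corrected: n/4 × [1 + √(1 + 4/(n·d))]² = 86.1, so 87 per arm, one short of the stated 88. At α = 0.05 the same formula gives 85.
- Dropout: 88/0.75 = 117.3, so 118 per arm and 236 in all. Centre sizes agree: 9 × 12 + 8 × 16 = 236.

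The one-sided 5% in the Sample size section gives 63 per arm (71 with correction), so the two-sided reading is used here.

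**2. Power of the chi-square as planned** (no continuity correction, α = 0.046259): Φ{[0.25 - 1.993·√(0.46875/n)] / √(0.4375/n)}.

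- n = 88 per arm: (0.25 - 0.1455)/0.0705 = 1.48, power 93.1%.
- n = 118 per arm: (0.25 - 0.1256)/0.0609 = 2.04, power 97.9%.

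The 90% target is met without adjustment.

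**3. Gain from adjustment, by simulation.** Layout: 17 centres of the stated sizes, blocks of 4, IMV mortality 75%, two-sided α = 0.046259, 2,000 trials per scenario (4,000 under the null). Prognostic strength is **assumed**:

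| Strength | Log odds ratio per SD, SAPS II | Log odds ratio per SD, PaO2/FiO2 | Centre SD (logit) |
|---|---|---|---|
| None | 0 | 0 | 0 |
| Weak | 0.5 | 0.2 | 0.3 |
| Moderate | 0.8 | 0.3 | 0.3 |
| Strong | 1.1 | 0.4 | 0.5 |

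Power (%), chi-square → logistic regression on continuous SAPS II and PaO2/FiO2:

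| N | True difference | Weak | Moderate | Strong |
|---|---|---|---|---|
| 176 | 25 points | 94.4 → 94.9 | 94.2 → 96.5 | 93.6 → 97.0 |
| 176 | 20 points | 78.8 → 81.1 | 79.2 → 84.4 | 78.8 → 87.2 |
| 176 | 15 points | 57.6 → 60.8 | 56.2 → 60.9 | 57.8 → 66.4 |
| 236 | 25 points | 98.6 → 99.1 | 98.3 → 99.0 | 98.0 → 99.4 |
| 236 | 20 points | 89.8 → 91.6 | 89.9 → 92.6 | 90.5 → 94.9 |
| 236 | 15 points | 66.9 → 69.8 | 67.8 → 73.8 | 71.0 → 78.8 |

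Subtracting, the gain is 0.5 to 3.4 points at the 25-point effect and 1.8 to 8.6 points at 15 to 20. With strength "none" it is about 0. A covariate-standardised risk difference gives nearly the same power as the logistic test. A Cochran-Mantel-Haenszel test by centre, without covariates, changes power by -0.4 to +1.0 point, so nearly all the gain comes from the patient-level covariates.

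**4. Type I error** (nominal 0.0463; simulation standard error √(0.0463 × 0.9537/4000) = 0.0033):

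| Test | Rejection rate under the null |
|---|---|
| Chi-square | 0.043–0.047 |
| Mantel-Haenszel by centre | 0.044–0.048 |
| Adjusted for SAPS II and PaO2/FiO2 | 0.042–0.048 |
| Logistic with centre fixed effects | 0.057–0.066 |

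With 12 to 16 patients per centre, the fixed-effects model rejects too often: even its lowest rate is about 3 standard errors above nominal.

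**The case against.** The strongest reply is that nothing is broken. The chi-square holds its error rate, corresponds to the two-proportion comparison on which the trial was sized, and exceeds its power target. Adjusted or centre-stratified supporting analyses may well be in a SAP that is not shown. All of that stands. What remains is that the article itself fixes which test is primary, and a more efficient one is available from data already collected.

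Four stronger readings are tempting and are not supported:

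- *The trial is underpowered because it does not adjust.* At the design effect it is not (93.1% or 97.9%).
- *Ignoring centre gives away power.* The change is about zero. The case for including centre is that the analysis should follow the randomisation.
- *Chance imbalance in severity makes the test wrong.* The error rate of the chi-square already allows for chance imbalance; adjustment is a matter of efficiency.
- *The PaO2/FiO2 cut at 100 isolates a sliver of patients.* If values were uniform over the eligible 85 to 170, 15/85 = 18% would fall below 100, but the document gives no distribution. The analysis is labelled exploratory. For a 25-point interaction with all 236 patients, power would be about 35% at an 18% share, 43% at 25%, 47% at 30% and only 54% with an even split, so it is weak wherever the cut falls.

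A fair caution concerns timing. Baseline data are recorded just after inclusion, and the participant timeline places randomisation at inclusion too. In an open-label trial, the document does not show that SAPS II is fixed before allocation is known. It does not show the opposite either, so this is a condition on the fix.

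**Conclusion.** The point holds as one of efficiency: the primary test is valid and adequately powered for 75% v 50%, but uses neither the randomisation strata nor the recorded severity measures. The benefit of adjusting is about 0.5 to 3.5 points of power at the design effect, about 2 to 9 points at a true difference of 15 to 20 points, and none if the covariates do not predict death. These sizes rest on the assumed prognostic strengths. The direction was the same in every prognostic scenario, and covariate adjustment did not inflate type I error. The change is worth making, but the trial is not unsound without it. The random-centre model and the combination of covariates with centre strata were not themselves simulated.

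**What to change.** Before any comparison by arm is seen, prespecify as primary a covariate-adjusted analysis of day-30 death:

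- Enter SAPS II and PaO2/FiO2 as continuous terms, and state that both values are those measured before randomisation.
- Report a standardised risk difference with its confidence interval. This keeps the marginal scale on which the trial was sized; a logistic odds ratio would be conditional on the covariates.
- Use the same analysis at both interim looks and at the final look.
- Account for centre by a random effect or Mantel-Haenszel-type stratification, not by centre fixed effects. Check the type I error of the chosen form by simulation before it is frozen.
- Keep the unadjusted chi-square as a sensitivity analysis.

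As a secondary suggestion, test the exploratory severity interactions with SAPS II and PaO2/FiO2 as continuous terms, and keep the cut-points of 60 and 100 for descriptive subgroup estimates.

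The cost is wording in the protocol or SAP, slightly more analysis work and reliance on a working model. No new variables, patients or visits are needed.

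### The primary analysis puts its 95% intervals on mortality frequencies, names no interval for the between-arm difference, and uses 0.05 and 95% although the final look is set at 0.046259

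*Protocol article*

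**What the plan says.** Three parts of the protocol article bear on the primary result.

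- **Statistical analysis, Primary endpoint.** "30-day mortality will be reported as frequency with the 95% confidence intervals" and "compared between the two groups using the χ^2^ test". The term treatment effect appears only for the interaction and subgroup analyses, and no measure is given for it.
- **Statistical analysis, opening paragraph.** "All tests will use a significance level of 0.05", with no exception for the primary test. The paragraph adds: "All analysis results and findings will be reported according to CONSORT statement recommendations".
- **Interim analysis.** "Sample sizes of 176 achieve 90% power to detect a difference of 0.25 between the group proportions of 0.50 and 0.75", two-sided at 0.05. Two interim looks and a final look use O'Brien-Fleming spending, with nominal levels 0.000207, 0.012025 and 0.046259. The stopping rule reads: "If the difference of the main outcome, mortality was found statistical difference between groups, then discontinuation ahead will be applied".

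**The concern.** **The estimate.** The trial is powered on a difference of 25 points, but the planned intervals belong to the mortality frequencies, most naturally one per arm. Two per-arm intervals do not show the uncertainty of the difference. They can overlap when the test is significant. In a null result they do not show directly how much benefit or harm remains compatible with the data.

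**The level.** The sequential design spends part of the 5% at the interim looks and leaves 0.046259 for the last one. The general 0.05 and the 95% intervals take no account of this. For a final p just under 0.05, the two sections give opposite conclusions on the primary endpoint, and the choice between them would be made with the result in view.

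**Early stopping.** The trial stops when a boundary is crossed, so the observed difference in a stopped trial is selected for being large. The article attaches no caution to it.

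**Working it through.** **1. The plan's own figures.** Inputs from Sample size and Interim analysis: rates 0.75 and 0.50, two-sided 0.05, 90% power, continuity correction, three looks, 25% dropout.

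- Pooled-variance size per arm: n = (1.960 + 1.282)² × 2 × 0.625 × 0.375 / 0.25² = 78.8.
- Three-look inflation of 1.012: 79.7.
- Continuity correction: (n/4) × [1 + √(1 + 4/(n × 0.25))]² = 87.6, so 88 per arm and 176 in total, as stated.
- Dropout: 88/0.75 = 117.3, so 118 per arm and 236 in total, as stated.
- Looks at equal thirds: the stated nominal levels correspond to |Z| = 3.710, 2.511 and 1.993. Simulated under no difference they give an overall two-sided error of 0.0500. The boundaries are sound.

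**2. Using 0.05 at the last look.** The first two looks together spend 0.0121.

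| Level at the last look | Critical value | Added at the last look | Overall type I error |
|---|---|---|---|
| 0.046259 | 1.993 | 0.0379 | 0.0500 |
| 0.05 | 1.960 | 0.0414 | 0.0535 |

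**3. A result on which the sections disagree.** Illustrative final data: 67/88 deaths (76.1%) on IMV and 55/88 (62.5%) on NIV.

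- Difference = 12/88 = 0.136. Pooled rate = 122/176 = 0.693.
- z = 0.136 / √(2 × 0.693 × 0.307 / 88) = 0.1364/0.0695 = 1.961, so p = 0.0498 (no continuity correction). This is significant at 0.05 and not at 0.046259.
- The unpooled standard error is 0.0688. The Wald 95% interval is 0.002 to 0.271 and excludes zero. The 95.4% interval is -0.001 to 0.273 and does not.

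**4. Per-arm intervals against the interval for the difference.** Rates of 0.75 v 0.60 with 88 per arm give p = 0.034.

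- Per-arm 95% Wald intervals: 0.660 to 0.840 and 0.498 to 0.702. They overlap.
- Difference: 0.150, standard error √(0.75 × 0.25/88 + 0.60 × 0.40/88) = 0.0697. The 95% interval is 0.013 to 0.287.
- At 95.4% it is 0.011 to 0.289. The widening is 1.993/1.960 = 1.017, or 1.7%.

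**5. Early stopping.** Simulation of the three-look rule with the stated nominal levels, a pooled z-test without continuity correction, and the naive difference with a Wald 95% interval. The article's 39 at each look is read as per group, because 118/3 = 39.3. Looks at 29/59/88 allow for 25% lost.

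| Truth | Looks per arm | Stops early | Mean difference if stopped | Mean over all trials | Naive coverage, all trials |
|---|---|---|---|---|---|
| 75% v 50% | 29/59/88 | 63% | 31 points | 26.5 points | 92.5% |
| 75% v 50% | 39/78/118 | 77% | 29 points | 26.4 points | 93% |
| 75% v 60% | 29/59/88 | 22% | 27 points | 15.9 points | 94% |
| 75% v 60% | 39/78/118 | 31% | 24 points | 16.0 points | 94% |

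With the continuity correction, early stopping at the design effect falls to 54% and 72%, with stopped means of 32 and 29 points.

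**6. What a sequentially adjusted estimate would change.** Stagewise median-unbiased estimates at a second-look stop:

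- 37/78 v 59/78 deaths: naive 0.282 (0.136 to 0.428), adjusted 0.280 (0.131 to 0.427).
- 26/58 v 44/58 deaths: naive 0.310 (0.141 to 0.479), adjusted 0.309 (0.138 to 0.478).

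A stop at the first look is left unchanged by construction.

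**The case against.** The strongest reply is that nothing is lost. The risk difference and its interval follow from two frequencies and two denominators. The article commits to CONSORT reporting and speaks of a treatment effect. The specific levels in Interim analysis can be read as overriding the general 0.05. A condensed article may also leave the effect measure and interval method to an analysis plan that is not shown.

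Much of this stands, and it rules out three stronger readings.

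- **That the plan yields no valid effect size.** It does yield one. Over all trials at the design effect, the naive difference is biased by about 1.5 points, with coverage of 92.5% to 93%.
- **That the trial should be expected to stop early.** This holds only near the 25-point effect taken from the earlier meta-analysis. At 15 points the figure is 22% to 31% without continuity correction.
- **That the plan is defective without a sequentially adjusted estimate.** The article does not call its intervals fixed-sample or exclude an adjustment. The median-unbiased correction moves a typical second-look result by about 0.2 points or less, so it does not cure the exaggeration.

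What the reply does not remove is the text itself. The article chose a reporting format for the primary endpoint and attached the intervals to the frequencies. It also set one level for all tests, which differs from the level it gives for the final look. A general reporting commitment settles neither the primary measure nor its level.

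**Conclusion.** The point holds as a matter of wording, with small numerical consequences. The primary paragraph gives intervals for mortality frequencies and none for the difference on which the trial is sized. The 0.05 and 95% conflict with the final nominal level of 0.046259. If 0.05 were used at the last look, the overall type I error would be about 5.35% instead of 5.0%, and any final p between 0.0463 and 0.05 would be judged differently by the two sections.

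This rests on reading the frequency intervals as per-arm, on looks at equal thirds, and on the two-sided difference test described in Interim analysis. Sample size instead speaks of non-inferiority with a one-sided 5% error and gives no margin. That is a separate conflict, but under that aim too the interval for the difference would be the quantity needed.

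Early-stop exaggeration is real but conditional: 4 to 6 points on average among stopped trials at the design effect. It calls for a plain caution beside the estimate.

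**What to change.** 1. **Statistical analysis, Primary endpoint:** state that the primary estimate is the risk difference in 30-day mortality, IMV minus NIV, with its confidence interval. At the final analysis use the level matching the last boundary: 1 - 0.046259 = 95.4%. Keep the per-arm frequencies as description.
2. **Statistical analysis, opening paragraph:** exempt the primary test from the general 0.05 and say that the nominal levels in Interim analysis govern it at every look.
3. **If the trial stops early:** report with the estimate that it comes from a stopped trial and tends to be too large. A median-unbiased estimate may be added but is optional.

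The cost is a few sentences and no new data. The interval becomes about 1.7% wider, and a final p between 0.0463 and 0.05 will not count as significant, which is what the stated boundaries already imply.
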